## **2 Statistical analysis**

---

### **2.1 Analysis principles**

- Data analysis will be performed according to an intention-to-treat analysis, that is, clusters will be analysed according to their randomised cross-over time irrespective of whether cross-over was achieved at the desired time.
- All tests are to be two-sided with a nominal level of  $\alpha$  set at 5%.
- Subgroup analyses (see Section 2.5.3) will be carried out irrespective of whether there is a significant treatment effect on the primary outcome. These analyses will also be unadjusted.
- No formal adjustments for multiplicity will be applied. However, the outcomes will be categorised by the degree of importance (primary vs secondary), and only a limited number of subgroup analyses are pre-specified. The results will be interpreted in this context.
- Analyses will be conducted primarily using SAS software (version 9.3 or above).

## 2.2 Data set analysed

The implementation intervention periods occurred on the following dates:

1. Concord Repatriation General Hospital (ED 1): 30/07/18 to 24/08/18
2. Royal Prince Alfred Hospital (ED 2): 27/08/18 to 21/09/18
3. Canterbury Hospital (ED 3): 24/09/18 to 19/10/18
4. Dubbo Base Hospital (ED 4): 22/10/18 to 16/11/18

Due to the cluster design, the group allocation (control or intervention) for a patient will be determined by the site and by the period during which they participated. All patients will be regardless of the interventions actually received, thus adhering to the ITT analysis principle. The different analyses periods are defined in Table 3. A patient will be counted in a period if the day of his/her ED presentation falls into that period.

| Periods | Dates                | ED 1 | ED 2 | ED 3 | ED 4 | Periods                         |
|---------|----------------------|------|------|------|------|---------------------------------|
| 1       | Jul 2017             | xxx  | xxx  | xxx  | xxx  | 12-month retrospective baseline |
| 2       | Aug 2017             | xxx  | xxx  | xxx  | xxx  |                                 |
| 3       | Sep 2017             | xxx  | xxx  | xxx  | xxx  |                                 |
| 4       | Oct 2017             | xxx  | xxx  | xxx  | xxx  |                                 |
| 5       | Nov 2017             | xxx  | xxx  | xxx  | xxx  |                                 |
| 6       | Dec 2017             | xxx  | xxx  | xxx  | xxx  |                                 |
| 7       | Jan 2018             | xxx  | xxx  | xxx  | xxx  |                                 |
| 8       | Feb 2018             | xxx  | xxx  | xxx  | xxx  |                                 |
| 9       | Mar 2018             | xxx  | xxx  | xxx  | xxx  |                                 |
| 10      | Apr 2018             | xxx  | xxx  | xxx  | xxx  |                                 |
| 11      | May 2018             | xxx  | xxx  | xxx  | xxx  |                                 |
| 12      | Jun 2018             | xxx  | xxx  | xxx  | xxx  |                                 |
| 13      | 01/07/18 to 29/07/18 | xxx  | xxx  | xxx  | xxx  | Core stepped-wedge trial        |
| 14      | 30/07/18 to 25/08/18 | xxx  | xxx  | xxx  | xxx  |                                 |
| 15      | 26/08/18 to 22/09/18 | xxx  | xxx  | xxx  | xxx  |                                 |
| 16      | 23/09/18 to 20/10/18 | xxx  | xxx  | xxx  | xxx  |                                 |
| 17      | 21/10/18 to 16/11/18 | xxx  | xxx  | xxx  | xxx  |                                 |
| 18      | 17/11/18 to 16/12/18 | xxx  | xxx  | xxx  | xxx  |                                 |
| 19      | 17/12/18 to 16/01/19 | xxx  | xxx  | xxx  | xxx  | 3-month follow-up               |
| 20      | 17/01/19 to 16/02/19 | xxx  | xxx  | xxx  | xxx  |                                 |

|  |                                      |
|--|--------------------------------------|
|  | Pre-implementation (control)         |
|  | During implementation (not analysed) |
|  | Post-implementation (intervention)   |

## **2.3 Trial profile**

The flow of patients through the study will be displayed in a CONSORT diagram.

## **2.4 Baseline comparisons**

Description of the baseline characteristics will be presented for each of the four EDs. This will be done by aggregating data collected over the 12-month retrospective baseline period. Discrete variables will be summarised by frequencies and percentages. Percentages will be calculated according to the number of clusters with available data. Continuous variables will be summarised by using mean and standard deviation (SD), and median and interquartile range (IQR, Q1-Q3).

In addition, we will investigate temporal trends in health service use outcomes across the 12-month retrospective baseline control period for each ED. This will be done by summarising each primary and secondary outcome for each month within each ED and displaying the estimates (proportion or mean) together with their 95% confidence intervals on a graph. Should a visual inspection of the longitudinal plots suggest an underlying temporal trend, we will only include data for the previous three months (periods 11 to 13) as the baseline period to be used for the main model. The visual assessment of temporal trends over the baseline period will be completed by fitting a regression (logistic or linear) to assess the significance of time (month) slopes. The linear model will include a fixed term for time (months) as a continuous variable and a random effect of ED to account for clustering.

## **2.5 Patients and clinicians' characteristics and baseline comparisons**

Description of the baseline characteristics will be presented by treatment period (i.e. pre-intervention or post-intervention). Discrete variables will be summarised by frequencies and percentages. Percentages will be calculated according to the number of patients in whom data are available. Continuous variables will be summarised by using mean and SD, and median and IQR (Q1-Q3). No adjustment for clustering will be applied when summarising baseline characteristics.

Baseline measures for all eligible low back pain presentations will be tabulated with at least the following variables outlined below:

- Age
- Gender
- Socioeconomic status
- ED Diagnosis
- Day of ED presentation

- ED presentation hour
- ED mode of arrival
- ED triage category
- Length of ED stay
- Proportion of presentations admitted to a hospital ward
- Length of stay in hospital ward

Characteristics of clinician participants will be tabulated with at least the following variables outlined below:

- Gender
- Age
- Main profession
- Country of professional training
- Clinical experience in main profession (years)
- Clinical experience in emergency medicine (years)
- Average number of low back pain patients seen per week

## 2.6 Analysis of the primary outcome

### 2.6.1 Main analysis

The primary endpoint is a binary variable indicating whether a patient received any lumbar imaging (yes/no). The primary analysis will be conducted using a logistic regression with a random effect for cluster (hospital ED), a random effect for clinician nested within cluster, a fixed effect indicating the group assignment of each cluster at each step and a fixed effect of time (each step). The model will be specified as follows:

$$\text{logit} [ P(Y_{ijk} = 1) ] = \alpha + \beta \text{Group}_{ij} + \delta_j + u_i + v_{ijk} + e_{ijk} \quad (1)$$

where:

- $Y_{ijk}$  denotes the outcome of subject  $k$  ( $k=1, \dots, m_{ij}$ ) in period  $j$  ( $j=1, 2$ ) within ED  $i$  ( $i=1, \dots, N$ ) where  $m_{ij}$  indicates the number of subjects in period  $j$  within ED  $i$
- $\alpha$  is the intercept
- $\text{Group}_{ij}$  is a dummy variable indicating group allocation during period  $j$  for cluster  $i$  with  $\text{Group}_{ij} = 1$  post-intervention, and  $\text{Group}_{ij} = 0$  pre-intervention
- $\beta$  is the parameter of interest estimating the treatment effect and where  $e^\beta$  is the odds ratio (OR)
- $\delta_j$  is a fixed period effect
- $u_i$  is a random cluster effect with  $u_i \sim N(0, \sigma_u^2)$

$v_{ijk}$  is a random clinician effect which is nested within cluster with  $v_{ijk} \sim N(0, \sigma_v^2)$   
 $e_{ijk}$  are individual-level errors following a binomial distribution

The effect of the intervention will be presented as the OR of receiving any lumbar imaging and its 95% confidence interval (CI). In case of convergence issues caused by the inclusion of two random effects, we will remove the random clinician effect and keep the random cluster effect.

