- During weeks 1 to 4, individual meetings with clinician participants will be scheduled as required to cover the key messages and principles outlined in the ACI model of care. There will be at least one educational outreach visit to each clinician in weeks 1 to 4 and they can request additional if they have any concerns. Clinician participants can also seek advice from clinical educators by email.

d) Develop audit and feedback focussed on study outcomes

- Each emergency department and clinician participant will receive at the first educational seminar session an emergency department level feedback on the 12-month retrospective data performance against the outcomes of this study (that is, imaging, opioids, inpatient admission rates).

- This audit and feedback approach will be repeated each month after the implementation of the model of care during the regular emergency staff meetings until the end of the follow-up period.
- Clinician participants at the Sydney Local Health District (SLHD) will be encouraged to use the SLHD Targeted Activity and Reporting System (STARS) to monitor the emergency department performance during and after the implementation period

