# 1 Study design

## 1.1 Overview

The Sydney Health Partners Emergency Department (SHaPED) trial used a stepped wedge cluster randomised controlled trial design to evaluate an implementation strategy of the Agency for Clinical Innovation (ACI) model of care for acute low back pain in emergency departments (ED). In this study design, clusters are randomised to cross from the 'control period' (i.e. unexposed to intervention) to the 'intervention period' at regular intervals (steps) until all clusters have crossed to the intervention under evaluation.

In the SHaPED trial, after a retrospective baseline period of 12 months prior to randomisation, the implementation strategy was sequentially rolled out, with a new ED receiving the implementation strategy every 4 weeks, until all EDs implemented the model of care. Then, all EDs were followed-up and monitored for three months. For the primary analysis, the 'intervention period' was defined as the post-implementation and follow-up periods. The 'control period' is defined as the 12-month retrospective and prospective baseline control periods. Table 1 below illustrates the SHaPED trial design.

| Table 1. Sydney Health Partners Emergency Department (SHaPED) trial design |      |     |     |     |     |     |      |     |     |     |     |     |     |     |     |     |     |     |      |     |  |
|----------------------------------------------------------------------------|------|-----|-----|-----|-----|-----|------|-----|-----|-----|-----|-----|-----|-----|-----|-----|-----|-----|------|-----|--|
| Steps
(clusters)                                                        | 2017 |     |     |     |     |     | 2018 |     |     |     |     |     |     |     |     |     |     |     | 2019 |     |  |
|                                                                            | Jul  | Aug | Sep | Oct | Nov | Dec | Jan  | Feb | Mar | Apr | May | Jun | Jul | Aug | Sep | Oct | Nov | Dec | Jan  | Feb |  |
| ED 1                                                                       |      |     |     |     |     |     |      |     |     |     |     |     |     | x   |     |     |     |     |      |     |  |
| ED 2                                                                       |      |     |     |     |     |     |      |     |     |     |     |     |     |     | x   |     |     |     |      |     |  |

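### The single treatment effect in SAP 2.6.1 is the intervention-period effect only if it is constant; otherwise it mainly reflects the first two post-implementation months

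*Combined protocol and SAP*

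**What the plan says.** SAP 2.6.1 fits a logistic model with a random ED effect, a random clinician effect (removed if the model does not converge), a fixed effect for each period and one group indicator. The coefficient β on that indicator "is the parameter of interest estimating the treatment effect".

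SAP 1.1 pools the post-implementation and follow-up months into one intervention period. On follow-up it says: "Then, all EDs were followed-up and monitored for three months". In Table 3 of SAP 2.2 the implementation cells are labelled "During implementation (not analysed"). The roll-out runs from "Concord Repatriation General Hospital (ED 1): 30/07/18 to 24/08/18" to "Dubbo Base Hospital (ED 4): 22/10/18 to 16/11/18", with one ED entering in each of periods 14 to 17.

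Protocol Appendix 3, item 4, concentrates seminars and outreach in weeks 1 to 4. Of the feedback component it says: "This audit and feedback approach will be repeated each month after the implementation of the model of care".

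The sensitivity analyses of the primary outcome are covariate adjustment (2.7.1) and counting the implementation period as intervention (2.7.2). No exposure-time term or time-averaged effect is specified.

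**The concern.** A single β assumes that the effect is the same in every month after implementation. The documents give reasons to doubt this in both directions: feedback continues monthly, so the effect could build, while teaching is front-loaded, so it could wane.

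The layout makes the assumption matter. With period effects fitted, information on β comes mainly from periods in which treated and control EDs are observed together, and there are two of these. In the later months every analysed ED is treated, so those months act largely as references for one another. A reader who takes the odds ratio as the average effect over the period in SAP 1.1 could be misled in either direction, and follow-up adds little to the headline result.

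**Working it through.** **Inputs.** From SAP 2.2: 4 EDs, 20 periods and 4 dropped cells, leaving 80 - 4 = 76. From SAP 1.3.3: 30% to 20%, ICC 0.1, 80% power; from SAP 2.1: two-sided 5%. Cell size is my assumption, taken from the 2016 volume in the protocol's sample-size section: 2650 / (4 × 12) ≈ 55 per ED-month, with equal EDs because no ED-level volumes are given.

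**1. Reproduce the plan's sample size.** I used the Hussey–Hughes variance with I = 4 EDs, T = 5 periods and no dropped cells:

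var = Iσ²(σ² + Tτ²) / [(IU - W)σ² + (U² + ITU - TW - IV)τ²]

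- U = 10, W = 30, V = 30.
- Within-ED variance = (0.3×0.7 + 0.2×0.8)/2 = 0.185.
- σ² = 0.185/96 = 0.00193; τ² = 0.185 × 0.1/0.9 = 0.0206.
- var = 0.000807/0.636 = 0.00127, so SE = 0.0356.
- 0.10/0.0356 - 1.96 = 0.85, which gives power of 80.2%.
- N = 4 × 5 × 96 = 1,920, as stated.

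**2. Where treated and control EDs coexist.**

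| Period | Control | Dropped | Treated (month since implementation) |
|---|---|---|---|
| 14 | EDs 2, 3, 4 | ED 1 | none |
| 15 | EDs 3, 4 | ED 2 | ED 1 (1) |
| 16 | ED 4 | ED 3 | ED 1 (2), ED 2 (1) |
| 17 | none | ED 4 | ED 1 (3), ED 2 (2), ED 3 (1) |
| 18–20 | none | none | all four |

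EDs 1 to 4 contribute 6, 5, 4 and 3 treated cells, 18 in all. By month 1 to 6 the counts are 4, 4, 4, 3, 2, 1.

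**3. Weights by hand at ICC 0.** Only periods 15 and 16 contribute. Each compares one ED with two, so they count equally. Month 1 gets 0.5×1 + 0.5×0.5 = 0.75, month 2 gets 0.5×0.5 = 0.25, and later months get 0.

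**4. Weights at ICC 0.1.** These are the first row of (X′V⁻¹X)⁻¹X′V⁻¹ for the group term, with categorical periods and a random ED intercept, summed by month since implementation:

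| Baseline | 1 | 2 | 3 | 4 | 5 | 6 |
|---|---|---|---|---|---|---|
| All 20 periods | 0.837 | 0.294 | 0.015 | -0.044 | -0.058 | -0.044 |
| Periods 11–13 (SAP 2.4 fallback) | 0.959 | 0.355 | 0.035 | -0.105 | -0.140 | -0.105 |

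With randomly unequal EDs, the month 1 weight on the full baseline ranges from about 0.74 to 0.94, and months 4 to 6 total -0.13 to -0.16. These are net weights summing to 1; month 1 is about 65% of the absolute weight. Deleting periods 18–20 moves the SE of β only from 5.26 to 5.31 points (full baseline).

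**5. What β would estimate** (full baseline; reductions in percentage points; the trajectories are my illustrations):

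- Constant 10: 10 × 1 = 10, no bias.
- Build 4/8/12/12/12/12: 0.837×4 + 0.294×8 - 0.131×12 = 4.1. Treated-cell mean: 168/18 = 9.3.
- Mild build, 8 then 10: 0.837×8 + 0.163×10 = 8.3. Mean: (32 + 140)/18 = 9.6.
- Wane 12/10/8/6/4/2: 10.04 + 2.94 + 0.12 - 0.26 - 0.23 - 0.09 = 12.5. Mean: 148/18 = 8.2.

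With the periods 11–13 baseline, the first build gives 2.9 against 9.3.

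**6. Logistic check** (large sample, fixed ED effects, full-effect OR = 0.25/0.429 = 0.58). A linear build to month 6 gives OR 0.93 against a cell-average 0.77. A wane from full to one-fifth of the effect gives 0.57 against 0.69. The pattern is the same.

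**7. Does SAP 2.7.2 cover this?** Counting implementation cells as intervention gives weights 0.67, 0.33, 0.11, 0, -0.03, -0.04, -0.03, starting with the implementation month. This is still front-loaded.

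**The case against.** Five points can be made for the plan.

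- The bias is conditional. The documents give no effect trajectory, and if the effect is constant β is exactly right. This stands, and the point is worded accordingly.
- Excluding the four-week implementation window already works as a transition period, so much of any build-up may be over by month 1. This makes a mild trajectory more plausible than a steep one (8.3 against 9.6 rather than 4.1 against 9.3). It does not change the weights.
- The weights rest on a linear model with equal EDs and no clinician effect, and negative weights need a non-zero ED effect. True, but the SAP itself assumes ICC 0.1, and at ICC 0 months 1 and 2 carry all the weight.
- No objective claims a sustained effect, and the lack of concurrent controls in periods 18–20 belongs to the design. Both are correct, but SAP 1.1 still defines the intervention period to include those months.
- A time-averaged estimate is imprecise: its 95% half-width is 1.96 × 6.3 ≈ 12 points, against a 10-point target. This also stands, although β's own half-width is 1.96 × 5.3 ≈ 10. It is a reason to call the added analysis supportive.

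A reader might infer that the trial will badly underestimate its effect. The documents do not support this: the direction is unknown, and across the building shapes tried β recovered 26% to 65% of the treated-cell average with steeper builds and 87% (8.3/9.6) with the mild one.

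**Conclusion.** The concern holds in conditional, two-directional form. β is the intervention-period effect if the effect is constant. If it varies with time since implementation, β mainly reflects the first two post-implementation months: net weights of about 0.84 and 0.29, then about 0, then -0.15 in total for months 4 to 6. With the three-month baseline these are 0.96, 0.36, 0.04 and -0.35. Nothing in SAP 2.7 would reveal the difference.

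It would go too far to say that β simply is a first-month effect, or that the primary analysis is invalid. The month 1 figure is a net share that depends on ED volumes the documents do not give, and the model is sound under its own assumption.

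The weights rest on the 20 periods of Table 3. The formula in 2.6.1 prints only two values of the period index, which does not match the table or its own per-step time effect. This is a should-fix matter of interpretation and sensitivity analysis.

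**What to change.** Keep the primary model and make three changes.

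- **SAP 2.7:** add a pre-specified sensitivity analysis that replaces the group indicator with categorical months since implementation (1, 2, 3, 4+), other terms unchanged. Report each category's effect, and the time-averaged effect with its CI beside β. State the averaging weights in advance; the treated ED-month counts 4, 4, 4 and 6 out of 18 are one choice. The linear version of this model is full rank on both baselines.
- **SAP 2.6.1:** state that β is the intervention-period effect only under a constant effect, and that otherwise it mainly reflects the first two post-implementation months.
- **SAP 2.6.1:** reconcile the period index with the 20 periods of Table 3.

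The cost is one extra model, a few sentences and a less precise estimate. With the inputs above, the time-averaged effect has SE about 6.3 points against 5.3 for β (7.6 against 5.6 with the three-month baseline), and the 4+ effect has SE about 8 to 10. Label it supportive rather than decisive.

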### **2.6.2 Treatment of missing data**

Given the ED dataset only records lumbar images that occurred, we will assume that a missing data point indicates that the corresponding procedure did not occur. The primary outcome (i.e. lumbar imaging) will therefore not contain any missing data. However, manual data extraction from patient's medical records were conducted for some secondary outcomes (i.e. opioid medication), since some EDs did not have electronic medication system (eMEDS) available. No imputation of secondary or patient reported outcomes will be performed.

### **2.6.3 Subgroup analyses**

The following subgroup analyses will be carried out for the primary outcome only:

- Age (<65 *versus* ≥65 years)
- Socioeconomic status (measured by patient's postcode - SEIFA)
- Australasian Triage Scale (ATS) category (ATS 1 to 5)
- SNOMED diagnosis codes (non-specific low back pain *versus* radicular low back pain)
- ED mode of arrival

The analysis for each subgroup analysis will be performed by adding the subgroup variable as well as its interaction with the intervention as fixed effects to the logistic regression model used for the primary analysis (see Section 2.6.1). Within each subgroup, summary measures will include raw counts and percentages within each treatment arm, as well as the OR for treatment effect with 95% CI. The results will be displayed on a forest plot including the P value for heterogeneity corresponding to the interaction term between the intervention and the subgroup variable.

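### The subgroup models hold the period and ED effects common to all subgroups, so the heterogeneity test is largely a before-after contrast and is biased if subgroup trends or ED-level subgroup gaps differ

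*Combined protocol and SAP*

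**What the plan says.** SAP 2.6.3 plans five subgroup analyses of the primary outcome: age, socioeconomic status, triage category, diagnosis group and mode of arrival. Each is fitted by "adding the subgroup variable as well as its interaction with the intervention as fixed effects" to the model of 2.6.1. In that model the time term "is a fixed period effect" with no subgroup index, and the ED effect is likewise common to all patients. The forest plot is to carry "the P value for heterogeneity corresponding to the interaction term between the intervention and the subgroup variable". No section lets the period or ED effect vary by subgroup, and the adjusted analysis in 2.7.1 adds covariate main effects only. Section 2.1 runs the subgroup analyses whatever the primary result and without multiplicity adjustment.

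Two other sections bear on the point. Section 1.1 sets the comparison: "The 'control period' is defined as the 12-month retrospective and prospective baseline control periods". Section 2.4 checks for baseline trends by "summarising each primary and secondary outcome for each month within each ED" and by a regression on month. If a trend is suspected, "we will only include data for the previous three months (periods 11 to 13) as the baseline period".

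**The concern.** The main effect is separated from calendar time because EDs cross over at different dates and period is in the model. The interaction asks a different question: did the gap between, say, older and younger patients change with the intervention? Period effects common to both subgroups drop out of that gap. What remains is the gap in control cells set against the gap in intervention cells, and the control cells are mostly much earlier. With implementation cells excluded, control and intervention cells coexist only in periods 15 and 16 (six of 76 cells).

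A similar problem arises between EDs. Early-crossing EDs supply more intervention and fewer control periods than late ones. If the subgroup gap differs between EDs, that imbalance also enters the interaction. The protocol enrols one rural and three urban hospitals, so equal gaps cannot be taken for granted.

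At stake is a claim that the strategy works in some patients and not in others, in a trial whose protocol plans to support wider roll-out if results are positive.

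**Working it through.** **The plan's own figure.** The documents give no precision figure for the subgroups. Their one relevant figure, 1,920 presentations, is reproduced by the Hussey-Hughes variance for 4 clusters and 5 periods with ICC 0.1, two-sided 5% and 30% versus 20%: 1,913 needed, power 0.802 at 1,920. It concerns the main effect and does not bear on this point.

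**1. Where the cells lie.** The layout is the 20-period table in SAP 2.2, with one effect per period (2.6.1 prints the index as j = 1, 2, which I read as each step) and each ED's implementation period dropped.
- Control: periods 1 to 13, 14, 15 and 16 for EDs 1 to 4. That is 58 cells, period sum 91 + 105 + 120 + 136 = 452, mean 7.8.
- Intervention: periods 15, 16, 17 and 18 to 20. That is 18 cells, sum 105 + 90 + 74 + 57 = 326, mean 18.1.
- Gap: 10.3 periods.

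**2. Bias from subgroup drift.** Assumed: no intervention effect in anyone, imaging flat at 26% in younger patients, and imaging in those aged 65 or over starting at 40% and rising linearly over the 20 periods (19 intervals). Then

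log ratio of ORs ≈ [logit(end) − logit(0.40)] × 10.32/19

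- 5 points: 0.205 × 0.543 = 0.111, ratio 1.12
- 8 points: 0.325 × 0.543 = 0.177, ratio 1.19
- 10 points: 0.405 × 0.543 = 0.220, ratio 1.25 (1.24 when fitted)

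**3. False-positive rate.** Volume: 2,650/(12 × 4) ≈ 55 per ED-month, from the protocol's 2016 count. With 30% aged 65 or over (assumed), the interaction SE is 0.168, so z = 0.66, 1.05 and 1.31. Φ(z − 1.96) + Φ(−z − 1.96) gives 10%, 18% and 26%. Simulations of the same scenario gave 10–11%, 18–19% and 25–27%, and 5.2–5.6% with no drift.

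A second set of fits used a true OR of 0.583 in both subgroups, 1,920 presentations and half the patients in each subgroup. An assumed annual trend OR of 0.7 in one subgroup splits the common OR into 0.67 and 0.49 (ratio 0.73), with 19% false rejection.

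**4. With the baseline cut to periods 11–13.** Control cells: 3 + 4 + 5 + 6 = 18, sum 36 + 50 + 65 + 81 = 232, mean 12.9, gap 5.2. The multiplier becomes 5.22/19 = 0.275. Ratios are 1.06, 1.09 and 1.12. With SE 0.21, rejection is 6%, 7% and 8%.

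**5. Would the cut be triggered?** An 8-point drift in 30% of patients moves the pooled rate by about 8 × 12/20 × 0.30 = 1.4 points over the baseline year. The pooled rate is 0.7 × 26% + 0.3 × 40% = 30.2%. Monthly ED estimates have 95% limits of about ±1.96 × √(0.302 × 0.698/55) = ±12 points. The regression on month is sharper but still weak: with 2,640 presentations and a month SD of 0.288 of the year, the SE of the 12-month change is √(0.302 × 0.698/2640)/0.288 = 3.1 points. Neither check would be expected to see it.

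**6. Bias from ED-specific gaps.** The mean step position of control cells is (13×1 + 14×2 + 15×3 + 16×4)/58 = 150/58 = 2.59. For intervention cells it is (6×1 + 5×2 + 4×3 + 3×4)/18 = 40/18 = 2.22. The difference is −0.364. If the subgroup gap rose by an assumed 0.23 log-odds from each ED to the next in step order, the spurious ratio would be about exp(−0.364 × 0.23) = 0.92. Subgroup-by-ED terms return it to 1.00 and raise the SE only from 0.168 to 0.172.

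**7. What time terms do.** Subgroup-by-linear-month restores a ratio of 1.00 and about 5% rejection under linear drift. If the 8-point drift instead plateaus by period 10, the linear model gives about 0.86; if it is a step at period 14, about 1.18. With subgroup-by-ED terms also in, the SE goes from about 0.17 to 0.26 (full baseline) or 0.21 to 0.46 (cut). Subgroup-by-period is far less precise: SE 0.60 against 0.19 with 4,000 presentations and equal subgroups, and at 1,920 it often failed by separation.

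**The case against.** The strongest reply is that the problem is conditional. Nothing in the documents shows or suggests a subgroup-specific trend, and without one (and with equal gaps across EDs) the planned test keeps its level. That stands, and it limits the point. A reader might infer that a spurious subgroup claim is likely, or that the planned P values are invalid as they stand. The documents support neither. A false finding is only more likely if subgroup trends differ, and even at a 10-point drift about three tests in four would not reject.

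Second, 2.4 already offers a safeguard. This stands in part: the cut removes about half of the bias, but its trigger works at ED level and would probably miss a trend confined to a minority of patients.

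Third, a reader might conclude that a time-adjusted interaction should replace the planned one. The numbers do not support that. For a true ratio of ORs of 1.71 (0.583 in one subgroup, no effect in the other), power falls from about 85–89% to 52–54%, and with the cut baseline from about 69–74% to 21–22%. The linear term can also over-correct a drift that levels off. This objection stands, and it is why the time terms belong in sensitivity models.

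Fourth, these are secondary analyses that 2.1 says will be read in context. That is true, but multiplicity is the only caution 2.1 gives; it does not mention time.

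**Conclusion.** The point holds in conditional form. As specified, the interaction rests mainly on an uncontrolled comparison across about 10 periods and assumes, without saying so, that calendar trends and ED effects are the same in every subgroup. Where that fails, the heterogeneity P value and subgroup ORs are biased. In the worked scenario, false heterogeneity is about 10% to 26% (ratios of ORs 1.12 to 1.24), or about 6% to 8% if the baseline is cut.

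These sizes rest on assumed drifts, subgroup shares and imaging rates, equal volumes across EDs and months, ED fitted as a fixed effect and no clinician effect. The last two simplifications do not alter the mechanism. The primary estimate does not depend on the subgroup models, so nothing here should be read as doubt about the main result.

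**What to change.** In SAP 2.6.3:

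1. Add subgroup-by-ED fixed effects to every subgroup model. The five-level triage variable needs 4 × 3 = 12 such terms, so state in advance how sparse levels will be pooled.
2. Beside that model, report a sensitivity model adding subgroup-by-linear-month, and one with subgroup-by-period where it can be estimated. Keep the subgroup-by-ED terms in both. Claim heterogeneity only if the estimates are consistent across models, judged on size and interval and not on significance in each.
3. Add plots of the 2.4 baseline trends by subgroup, and say that the unadjusted interaction assumes a common trend.

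The cost is SAP wording and a few extra fits. The first change costs almost no precision for a binary subgroup. The time-adjusted models cost a good deal (SE about 0.17 to 0.26, or 0.21 to 0.46 with the cut baseline), and the linear version removes only roughly linear drift. Some real subgroup differences will therefore be reported as unconfirmed.
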